# Study on psychoeducation enhancing results of adherence in patients with schizophrenia (SPERA-S): study protocol for a randomized controlled trial

**DOI:** 10.1186/1745-6215-14-323

**Published:** 2013-10-07

**Keywords:** Randomized controlled trial, Schizophrenia, Psychoeducation, Falloon’s method, Adherence to pharmacotherapy, Family, Caregiver

## Abstract

**Background:**

Poor adherence to pharmacotherapy negatively affects the course and the outcome of schizophreniaspectrum psychoses, enhancing the risk of relapse. Falloon and coworkers developed a Psychoeducation Program aimed at improving communication and problem-solving abilities in patients and their families. This study set out to evaluate changes in adherence to pharmacotherapy in patients diagnosed with schizophrenia-spectrum psychoses, by comparing one group exposed to the Falloon Psychoeducation Program (FPP) with another group exposed to family supportive therapy with generic information on the disorders.

**Methods:**

340 patients diagnosed with schizophrenia and related disorders according to standardized criteria from 10 participating units distributed throughout the Italian National Health System (NHS), will be enrolled with 1:1 allocation by the method of blocks of randomized permutations. Patients will be reassessed at 6, 12 and 18 months after start of treatment (duration: 6 months).

The primary objective is to evaluate changes in adherence to pharmacotherapy after psychoeducation. Adherence will be assessed at three-month intervals by measuring blood levels of the primary prescribed drug using high pressure liquid chromatography, and via the Medication Adherence Questionnaire and a modified version of the Adherence Interview. Secondary objectives are changes in the frequency of relapse and readmission, as the main indicator of the course of the disorder.

Enrolled patients will be allocated to the FPP (yes/no) randomly, 1:1, in a procedure controlled by the coordinating unit; codes will be masked until the conclusion of the protocol (or the occurrence of a severe negative event). The raters will be blind to treatment allocation and will be tested for blinding after treatment completion. Intention-to-treat will be applied in considering the primary and secondary outcomes. Multiple imputations will be applied to integrate the missing data. The study started recruitment in February 2013; the total duration of the study is 27 months.

**Discussion:**

If the psychoeducation program proves effective in improving adherence to pharmacotherapy and in reducing relapse and readmissions, its application could be proposed as a standard adjunctive psychosocial treatment within the Italian NHS.

**Trial registration:**

Protocol Registration System of ClinicalTrials.gov NCT01433094; registered on 20 August 2011; first patient was randomized on 12 February 2013.

## Background

Schizophrenia and its related psychoses are severe mental disorders with a high impact in terms of disability and poor quality of life. The clinical course of schizophrenia is typically one of highly recurrent acute episodes with chronic impairment of social, vocational and personal wellbeing [1-3]. Prevalence of schizophrenia in the general population is 0.5 to 1%, with a higher risk and poorer outcome among males than females [4].

The costs for patients, their families and society are huge, and largely generated by the direct cost of care, especially hospitalization [5-7]. Even higher costs arise from lost productivity (unemployment of patients and absence from work by the relatives who care for them), informal care, criminal justice service involvement, and social security expenditure [8,9].

Poor adherence to therapy negatively impacts on the course and the outcome of schizophrenia, enhancing the risk of relapse, hospital admission and readmission, and family burden [10]. Non-adherence to pharmacotherapy in patients diagnosed with schizophrenia is 41 to 50% [11,12] and is predictive of a higher risk of relapse and a readmission rate up to five times higher than in adherent patients [13].

Currently, pharmacotherapy is the most important therapeutic intervention in the treatment of schizophrenia-spectrum psychoses. Higher adherence to pharmacotherapy is expected to favor a better course of the disorder, and specifically to reduce the risk of relapse and readmission, both of which heavily increase the burden of the disorder and are a great cause of distress, particularly after compulsory admission.

In recent years, many educational programs have been aimed at improve knowledge of the disorder, its symptoms, course and outcome, and the availability of treatment, and have focused specifically on the patients and their families [14-17].

Psychoeducational programs were developed to improve adherence to pharmacotherapy by reducing irrational beliefs towards drugs and their side effects, increasing tolerance to the inevitable and unwanted effects, and promoting coping strategies and problem-solving skills to help face everyday problems associated with the disorder. Studies on the real effectiveness of these programs have found protective effects against the risk of relapse and on the probability of readmission, with medium effect-sizes: Cohen’s d = 0.18 (95% CI = 0.13 to 0.49) and d = 0.58 (95% CI = 0.27 to 0.89), respectively [16]. A 2011 meta-analysis including 5,142 participants from 44 independent trials conducted from 1998 to 2009 confirmed the effectiveness of psychoeducation in reducing relapse and readmission [18]. Participants receiving psychoeducation were also found to be more satisfied with mental health services and reported a better quality of life.

More complex intervention models involve both the patients and their families, because the disorder is chronic from its onset and can cause a heavy burden on the family: the patient is unlikely to preserve a reasonable level of autonomy and independence without the support of his/her relatives. For this reason, psychoeducation programs involving the family are more likely to produce positive results on the course of the disorder [16].

Falloon and co-workers were among the first to develop a model of intervention in schizophrenia centered on the psychoeducation of the patients and their families [19,20]. Falloon’s model included sessions aimed at helping patients and their families recognize early stressful events and early indicators of the risk of stress-induced relapse; sessions aimed at the development of optimal adherence to pharmacotherapy; and sessions aimed at improving coping strategies and problem solving in everyday life [20]. This method proved effective following the first evaluation: at the two-year follow-up, cumulative relapse rates markedly differed between controls and the interventional group (83% versus 17%, respectively), and family therapy according to Falloon’s model resulted in fewer hospitalizations, improvement in patients’ social functioning, and lower levels of family burden and distress [19]. Past studies on Falloon’s model did not investigate adherence to pharmacotherapy in detail but concentrated on the course of the disorder and, specifically on the risk of relapse and readmission. Several more studies confirmed the effectiveness of this method on the risk of hospitalization, family burden and patient’s social functioning [20] but did not report clear evidence of effects on adherence, a result expected on the theoretical basis of the model and supported in small-sample studies carried out in specialized academic settings [21]. The results of these latter studies cannot be extended to the General Hospital Psychiatric Units (GHPUs) operating in the Italian National Health System (INHS).

Currently, expert consensus guidelines assign family psychoeducation a high second-line rating and recommend it to address adherence problems in patients with severe mental disorders [22]. In the INHS, family psychoeducation is rarely provided to patients and their families, with the exception of academic settings [23]. There is evidence of an inverse relationship between the availability of community-based mental health care and the need status of schizophrenic patients: the fewer out-patient and rehabilitation services available, the more unmet needs there were [24]. Improving the effectiveness of treatment offered to patients who have been diagnosed with schizophrenia is also likely to reduce the stigma of schizophrenia [25], which is barely affected by the small increase in public understanding of the biological correlates of mental illness [26].

### Aims

This study specifically set out to investigate the effectiveness of Falloon and co-workers’ Psychoeducation Program (FPP) and to evaluate its feasibility as part of the standard care setting provided by the INHS. The FPP will be compared to a control group, and randomized to a treatment with generic information on the disorders administered with the same frequencies as the FPP (Generic Treatment (GT)). We foresee that the FPP will be effective in improving adherence to pharmacotherapy in the exposed group when compared to the non-exposed group, and we also expect that the FPP will reduce the risk of relapse and readmission in the exposed group, by maintaining its effects at both six-and twelve-month follow-ups. Positive results would imply the importance of applying the FPP in all INHS settings, and the need of exploring its potential in other classes of psychosis, such as affective psychoses, which are also burdened by high personal, family and social costs.

A secondary goal of the study is the production of a manual to be used in the training and assessment of the professional staff involved in the treatment of patients diagnosed with schizophrenia-spectrum psychosis.

The primary outcome of the study, adherence to therapy, will be measured through a triple approach: a scaled self-report questionnaire, a four-query interview and, for the first time, the blood levels of the primary prescribed drug (to be measured by a specialized pharmacology unit with extensive experience in this type of studies). In this way, we will be able to validate the simpler instruments of measurement, such as the self-report or interview, with an objective, gold-standard method (blood levels of the therapeutic compound), a practice rarely used in past studies on adherence to therapy in patients with psychosis [27]. If one or both of the simpler, self-report instruments of assessment prove to be valid enough to differentiate adherent from non-adherent or partially adherent patients, the study will produce add-on information on easy-to-be-administered tools, to be generalized for future related studies.

The participating INHS centers are distributed across the country: we foresee the participation of ten enrolling units from nine large administrative regions of north, central and south Italy, to include both GHPUs and University Psychiatric Clinics (UPCs), six of them already having experience with the FPP. The heterogeneity of the participating units can be seen as a limit of the study, when considered in terms of intra-cluster variance (which we took into account in statistical power analysis on sample size, with appropriate corrections). However, it can represent an advantage, too, allowing for the exploration of the feasibility and effectiveness of the FPP in different settings, especially those operating in GHPUs, which have traditionally been exposed to a higher workload than academic centers where the FPP has more often been tested thus far.

## Methods/design

### Overview

This study is supported by the Italian Medicines Agency (Agenzia Italia del Farmaco) - grant for SPERA-S: Study on Psychoeducation Enhancing Results of Adherence in Schizophrenia (FARM892ZXE) (see Acknowledgements for details on the contract of financing).

The institutional review boards of both the university that coordinated the study and of the participating centers approved the study’s protocol which complies with the provisions of the 1995 Declaration of Helsinki (as revised in Tokyo, 2004).

In this study, the FPP will be compared to a treatment providing general information on psychosis GT administered with the same frequency as the FPP. The study will be randomized and blinded for the assessment: raters will be not informed about whether patients are in the FPP or GT groups. Inevitably, the therapists providing the treatment will know their patients’ treatment status.

The study will enroll adult patients diagnosed with psychosis in the spectrum of schizophrenia from ten participating units distributed throughout INHS territory. The sample will be randomized in an exposed group and an unexposed group, with 340 patients overall enrolled, with a 1:1 allocation ratio.

### Eligibility criteria

#### Inclusion criteria

Patients will be enrolled when they have a diagnosis of psychosis in the spectrum of schizophrenia according to the International Classification of Diseases - tenth edition (ICD-10: codes F20 to F29) and have been in contact with the unit for at least 24 months; admitting ages vary from 18 to 55 years old. Enrolled patients will be randomly allocated to FPP treatment (yes/no) with a rate 1:1, via a procedure controlled by the coordinating unit; codes will be masked until the conclusion of the protocol (or the occurrence of a severe negative event). Randomization will be carried out by the method of blocks of randomized permutations (to preserve balancing between the exposed and the non-exposed groups). Randomization will be stratified by location, due to the study’s multisite nature.

#### Exclusion criteria

Exclusion criteria are mental retardation or any severe cognitive impairment; psychosis due to substance abuse or to a medical condition; affective psychosis; co-morbid substance dependence; patient does not understand Italian; pharmacotherapy with depot. Inability or unwillingness to provide informed consent are additional exclusion criteria (see Table 1 for details).

**Table 1 T1:** Eligibility criteria

Inclusion criteria	Diagnosis of psychosis in the spectrum of schizophrenia (ICD-10: F20 to F29)
	Contact with the unit for at least 24 months
	Admitting ages varying from 18 to 55 years
Exclusion criteria	Mental retardation, or any severe cognitive impairment
	Psychosis due to substance abuse or to a medical condition
	Co-morbid substance dependence
	Patient does not understand Italian
	Pharmacotherapy with depot
	Inability or unwillingness to provide informed consent

### Recruitment and baseline procedures

Patients will be enrolled in the clinical setting, which includes both GHPUs and UPCs.

To rationalize the training and quality-control procedures for the FPP and GT therapists (two for each participating unit) and the assessors (one for each unit), a Training and Quality Control Center will be established in Cagliari, the site of the coordination unit. This Center will train the assigned therapists in FPP and GT and will also train the assessors in the administration of the psychometric measures. On a regular six-month basis, the Center will organize meetings to verify the course of the study.

The Coordination Center will manage the procedures of treatment allocation and will coordinate the study, the statistical analysis, the storage of data, the training of the assessors involved in the patients’ evaluation and of the therapists involved in the FPP and GT. The Coordination Center with two units from the University of Cagliari (Center for Research and Treatment in Mental Health and Pharmacological Unit) will monitor data recording and storage, quality assessment of FPP and GT, and quality assessment of the training for assessors and therapists.

A Steering Committee (the principal investigator plus another member of the Coordination Center, a member from the Monitoring Unit, a member from the Statistics Unit, and three members elected by the enrolling units) will coordinate the use of the database for publications. A centralized laboratory (Pharmacological Unit, University of Cagliari) will analyze the blood levels for drugs in the samples received from all participating units.

### Timing

In the first three months of the study, the Coordination Center and all directors of the participating units will check the organization of the study, the assessment methodology, the training of the assessors and their inter-rater agreement.

As far as the investigational trial is concerned, we foresee three months for the enrollment of the patients; six months for the subsequent exposition to the FPP of the patients allocated to treatment (the exposed group), or same-length GT for the unexposed group; there will be subsequent six-month and twelve-month follow-ups to verify whether the immediate benefit of FPP, if any, is maintained after the conclusion of the FPP treatment. Patients will be evaluated at entry (t0), at the conclusion of the treatment (both exposed and unexposed) (t1), after six months of follow-up (t2) and after twelve months of follow-up (t3). The final report will be made within six months of the conclusion of the study, but initial reports will be prepared six months after the start (see Figure 1).

**Figure 1 F1:**
[figure not shown]
Flowchart of participants during the trial.

### Randomization procedures and bias-minimization methods

All patients will be randomized in the exposed (FPP) or the unexposed (GT) group with a 1:1 allocation ratio in each unit, as each unit is expected to participate in the enrollment of both groups. Randomization will be carried out by the method of blocks of randomized permutations (to preserve balancing between the exposed and the non-exposed groups). Randomization will be stratified by location due to the multisite nature of the study. Correctness of the randomization procedure will be monitored at regular intervals.

### Allocation concealment

Block size will be specified by the Coordination Center and will not be revealed to any researcher or staff until the end of the enrollment period.

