### Blinding

This study will implement a complete separation of treatment and assessment to allow for a single blind design of assessment. Therefore, therapists will not be involved in the assessment of the treatment outcome, and raters will not be allowed to hold treatment sessions. Patients will be informed about their treatment allocation by the therapist, and only therapists will receive information about group allocation. Discussions about patients enrolled in the study will be not allowed between raters and therapists, as per instructions given during staff training.

The raters will have to complete a ‘blindness protocol’ at the end of the study. Any unintentional disclosure of the treatment condition will therefore be hopefully documented. Further, the raters will be asked to guess the study condition of the patient after the end of the study. Among all documented guesses, the rate of correct guesses should not significantly differ from chance (that is, 50%). The main outcome of the study is adherence to the prescribed therapy, and one of the indicators is the measurement of blood levels of the primary prescribed drug, which is independent from the assessment carried out by the raters. It is unlikely that any personal opinion of the raters on the presumed superior effectiveness of the FPP over GT will influence the measurement of blood levels of the primary prescribed drug. However, we are interested in knowing whether any bias might have occurred in the blinding, whether by unintentional disclosure of the treatment condition or because the personal opinion of the raters led them to guess the patients’ allocation to the treatment modality.

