### Ethical considerations

The FPP is not expected to produce relevant somatic side effects but it can produce unwanted or unforeseen effects, such as an increase in the intra-family level of conflict. To maximize safety for the patients, before randomization each patient will be evaluated on his or her risk of unwanted or unforeseen effects attributable to exposure to the FPP.

The therapists involved in the administration of the FPP and GT will be monitored to minimize any improper method of administration of the protocol of treatment; assessors will also be trained and monitored to avoid dispersion of information, thus violating the guaranteed criterion of good faith in case of patients’ disclosing sensitive information. Data recording and storage will comply with the privacy law in force, and informed consent for information recording will be obtained from each patient.

Participation in the study is voluntary and written informed consent is obtained. Before enrollment, participants will receive both verbal and written assurance that they can withdraw from the trial any time, with no consequence for their continued treatment. Patients unable to give informed consent in an appropriate way or who refuse to participate in the study will not be enrolled.

The Training Center is committed to monitoring the quality of assessment and of the administration of the FPP procedures, on a three-month basis.

A paradoxical, unintended effect of greater adherence to pharmacotherapy is the potential increase of the somatic side effects of the prescribed drugs. Indeed, there is some indirect evidence that this can actually occur [66]. To limit this paradoxical effect, patients will be closely monitored for side effects and somatic conditions on a three-month basis or as needed. It is expected that, following improvement in the response to the therapy as a result of greater adherence to pharmacotherapy, the therapist will decrease dosage of the prescribed drugs. This specific change will be checked at assessment and a reduction of dosage of the prescribed drugs and of poly-pharmacotherapy is among the secondary outcomes of the study.

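### The block size is kept secret only until enrolment closes, although blinded ratings continue for about 18 more months

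*Protocol article*

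**What the plan says.** All references are to the protocol article.

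- **Method (Randomization procedures and bias-minimization methods).** "Randomization will be carried out by the method of blocks of randomized permutations", and "Randomization will be stratified by location due to the multisite nature of the study". Allocation is 1:1 within each unit.
- **Secrecy of the block size (Allocation concealment).** The rule reads: "Block size will be specified by the Coordination Center and will not be revealed to any researcher or staff until the end of the enrollment".
- **Secrecy of the codes (Inclusion criteria).** The coordinating unit controls allocation and "codes will be masked until the conclusion of the protocol (or the occurrence of a severe negative event"). Ethical considerations adds that only the Coordination Center holds the codes, which stay concealed until the end of the study.
- **Who knows the arm (Blinding).** "Patients will be informed about their treatment allocation by the therapist, and only therapists will receive information about group allocation". Raters are blind, and raters and therapists may not discuss enrolled patients. The section accepts that unintentional disclosure can occur. It has raters document it and guess each patient's arm at the end, and the guesses are compared with 50%.
- **Who rates and when (Recruitment and baseline procedures; Timing; Table 3).** Each unit has one assessor. Ratings take place at t0, t1 (end of the six-month treatment), t2 and t3 (six and twelve months later). Enrolment is planned to last three months.

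**The concern.** The block size and the allocation codes belong to the same concealed information, yet the block size has an earlier expiry date, with no reason given. When it expires, most or all post-baseline ratings are still to come.

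Knowing the block size does not unblind anyone. It makes a leak more informative, because in a balanced block the arms of some members constrain the arms of the others. Patients know their own arm and meet the rater repeatedly, so occasional leaks are realistic. One assessor per unit who rates every patient at t0 will also know roughly the order in which patients entered.

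At stake is the blind for the clinician-rated measures. BARS is an interview and contributes to the dichotomous adherence index. BPRS and PANSS define relapse, and CGI defines one of the safety endpoints. The planned test of rater guesses against 50% would be affected too, since some correct guesses could come from block arithmetic instead of from disclosure of that patient's arm.

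**Working it through.** **Time still to be rated blind.** From Timing: 6 months of treatment + 12 months of follow-up = 18 months after the last patient enters. With enrolment completed in the planned three months, even the first patient's t1, at six months, falls after enrolment closes. If enrolment runs longer, some early ratings precede the release, but the last patients still have all of t1 to t3 ahead.

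**Inputs not in the article.** The block size is not given; sizes 2 and 4 are used for illustration. The share q of allocations accidentally known to the rater is not given either; 0.05, 0.25 and 0.5 are shown. Leaks are taken as independent between patients, and the rater is taken to know the randomisation order within the site exactly. The last assumption is generous, so the results are upper limits.

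**No leak (q = 0).** The rater knows the block size but no assignment. Each patient is equally likely to be in either arm, so a guess is right 50% of the time.

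**Further patients who become certain.**
- Size 2: an undisclosed patient is known if the one partner is disclosed. Probability = q.
- Size 4: an undisclosed patient is known if both members of the opposite arm are disclosed. Probability = q × q.

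**Best-guess accuracy for an undisclosed patient.**
- Size 2: q × 1 + (1 − q) × 0.5 = (1 + q)/2.
- Size 4: the other three members comprise one of the same arm and two of the opposite arm. With none disclosed the guess is right with probability 1/2, with one disclosed 2/3, with two disclosed 2/3 on average, and with three disclosed 1. Accuracy = (1 − q)³ × 1/2 + 3q(1 − q)² × 2/3 + 3q²(1 − q) × 2/3 + q³.
- At q = 0.25, size 4: 0.4219 × 0.5 + 0.4219 × 0.6667 + 0.1406 × 0.6667 + 0.0156 = 0.602.

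| q | Certain, size 2 | Certain, size 4 | Best guess, size 2 | Best guess, size 4 |
|---|---|---|---|---|
| 0.05 | 5% | 0.25% | 52.5% | 52.4% |
| 0.25 | 25% | 6.25% | 62.5% | 60.2% |
| 0.5 | 50% | 25% | 75% | 68.8% |

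At q = 0.5 the blind has already failed directly for half the patients, so the lower rows show the mechanism more than a likely case.

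**The case against.** The defence has several good points.

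- **Secrecy until a date is not scheduled disclosure.** The sentence sets the minimum period of secrecy and does not say that raters will be told the size afterwards. This stands: the plan permits the release but does not order it.
- **Block size is not the code.** The codes stay masked to the end, so the two statements do not strictly contradict each other. This also stands. The mismatch is one of expiry dates.
- **Deduction needs a leak and the order.** Rater–therapist discussion is forbidden and disclosures are to be documented. At a low leak rate the added information is trivial (0.25% of remaining patients at q = 0.05, size 4). This stands and keeps the point small.
- **Some outcome data are protected.** Blood levels do not depend on the rater, and MARS is self-report. True, but the dichotomous adherence index uses the self-report or the interview, and relapse rests on rated symptoms.

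A reader might also infer something stronger: that one fixed block size is used at each site, that staff can therefore predict assignments, and that the evaluation described under Ethical considerations ("before randomization each patient will be evaluated on his or her risk of unwanted or unforeseen effects attributable to exposure to the FPP") lets them enrol selectively. The documents do not support this. The singular term for block size is generic, and a condensed article may leave fixed or varying sizes to the full protocol. Allocation is central, with masked codes and a size hidden throughout enrolment. Therapists know the assignments, but nothing says that they enrol patients, and no listed exclusion arises from the risk evaluation. Varying the sizes would also change little overall. For 34 patients per site (340/10), an observer who sees every earlier assignment guesses correctly about 70% of the time with fixed blocks of 4 and 68% with sizes drawn at random from 4, 6 and 8. Varying sizes mainly remove near-certain assignments: about 31% if a fixed size of 4 is known, against about 2%.

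**Conclusion.** The point holds for the release date only. Protection of the block size lapses about 18 months before the last blinded rating, without a stated purpose and earlier than protection of the codes. By itself the lapse reveals nothing. Combined with accidental disclosures and knowledge of the enrolment order, it could make a further 0.25% to 5% of the remaining patients certain at q = 0.05, or 6% to 25% at q = 0.25, for block sizes 4 and 2 respectively. These figures rest on assumed block sizes, assumed leak rates and exact knowledge of the order. The likely effect is a slight weakening of the blind for BARS, BPRS, PANSS and CGI and of the end-of-study guess test. Severity is low: this is a free improvement. Neither predictable allocation during enrolment nor selective enrolment has been shown.

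**What to change.** In Allocation concealment, move the end of secrecy from the close of enrolment to the point at which the last t3 assessment and the blinding assessment are complete and the database is locked. This aligns it with the masking of the codes in Inclusion criteria and Ethical considerations. It changes one sentence and needs no patients, staff or new system. Recruitment was ongoing when the article was written, so the change could still take effect.

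As a separate clarification, state whether block sizes are fixed or varying, without naming the sizes. If they are fixed, the Coordination Center could vary them for patients not yet randomised. This would remove near-certain assignments, at the price of a slightly larger possible imbalance per site (at most half the largest block).
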